Lifestyle modification, including physical activity, is one of the key recommendations for secondary prevention for patients with CVDs [13]. A systematic review and meta-analysis of 85 randomized controlled trials (RCTs) that included people with CHD reported that engaging in physical activity contributes to a substantial reduction in all-cause mortality, cardiovascular mortality, recurrent cardiac events, and improvements in health-related quality of life (HRQoL) [14]. However, inadequate physical activity is common among people with CHD in both developed and developing countries, and its prevalence ranges from 56.7% (Sri Lanka) to 83% (United States) [15, 16].

With the increasing morbidity and mortality rate from CHD, especially in low- and middle-income countries, secondary prevention including exercise-based CR plays an important role in improving the prognosis of patients with CHD [7, 17]. High prevalence of physical inactivity, unhealthy dietary practices, poor control of blood glucose, blood pressure (BP), blood lipid, and body weight (BW) was found among patients with CHD in the world, as well as in Sri Lanka [16, 18–20]. Therefore, a culturally appropriate intervention must be designed and implemented using a theoretical framework to improve the physical activity level, exercise self-efficacy, and cardiovascular risk factors in patients with CHD in Sri Lanka.

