### Sample size estimation

The sample size estimation is based on the primary outcomes of the study, namely, the physical activity level. Referring to the findings of the literature review, the effect size on improving physical activity is from 0.5 [25] to 0.8 [26]. Therefore, the smallest effect size of 0.5 [25] will be considered in calculating the sample size for this study. To achieve a power of 1-β = 0.8 with a significance level of 0.05 (two sides) and account for 14% of the attrition rate [27] of the previous study, a total of 150 participants will be recruited in this study.

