#### Primary outcomes

*Physical activity*. The primary outcome of the study is a behavioral change, which is physical activity. Physical activity refers to body movements that result in energy expenditure [39]. The International Physical Activity Questionnaire Short Form (IPAQ-SF) will be used in collecting the self-reported time spent in walking, moderate, and vigorous activities lasting at least 10 min, and time spent in sitting using the seven items [40]. The original English version of IPAQ-SF demonstrated high reliability with test-retest reliability ranging from 0.32 to 0.88 with more than three-quarters of studies showing a value greater than 0.65 [40]. The validated Tamil version of IPAQ-SF will be used in assessing the self-reported time spent in walking, moderate and vigorous-intensity activities, and sitting in this study.

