#### Data analysis

Data will be analyzed using SPSS version 22.0 statistical software with a 5% significance level (two-sided; SPSSINC., CHICAGO, IL, USA). Data will be analyzed using descriptive and inferential statistics. Descriptive statistics with mean, standard deviation, range, frequency, and percentage will be used to describe the participants’ socio-demographic characteristics and clinical data. The normality of the data will be tested using the skewness and kurtosis statistics and graphically analyzed by normal Q-Q plots. An independent t-test will be used to compare the baseline characteristics of the intervention and control group for continuous variables while the Chi-square test will be used for categorical variables. The generalized estimating equation model will be used to test the hypotheses, and determine the significant differences across different time points (effect of time, group, and time x group interaction) with adjustment for potential confounding variables to obtain a more precise estimation of the intervention effect. By clinical judgment and statistical incomparability at baseline, the potential confounders will be selected in this study. Intention-to-treat analysis will be used as an approach in analyzing all participants in the final analysis according to the original assigned group, irrespective of the treatment received. If these assumptions are not met, the equivalent non-parametric statistics will be used to analyze the data.

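### As worded, an undefined normality check may replace the primary adjusted GEE with unnamed non-parametric tests after the data are seen

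*Protocol article*

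**What the plan says.** All of the following is in the protocol article.

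- **Outcome** (Primary outcomes): "The International Physical Activity Questionnaire Short Form (IPAQ-SF) will be used in collecting the self-reported time spent in walking, moderate, and vigorous activities". The measure is therefore non-negative reported time. No mean, SD or distribution is given.
- **Check** (Data analysis): "The normality of the data will be tested using the skewness and kurtosis statistics and graphically analyzed by normal Q-Q plots". No cut-off is stated, nor which variables or visits are checked.
- **Baseline comparisons** (Data analysis): an independent t-test for continuous variables and a chi-square test for categorical ones.
- **Hypothesis test** (Data analysis): "The generalized estimating equation model will be used to test the hypotheses, and determine the significant differences across different time points", with effects of time, group and their interaction, and "with adjustment for potential confounding variables to obtain a more precise estimation of the intervention effect".
- **Fallback** (Data analysis, last sentence, directly after the intention-to-treat statement): "If these assumptions are not met, the equivalent non-parametric statistics will be used to analyze the data". No replacement test is named.
- **Design basis** (Sample size estimation): "the smallest effect size of 0.5 [25] will be considered in calculating the sample size for this study".

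**The concern.** Three features of the fallback work against the primary analysis.

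1. **The trigger does not match the model.** A GEE specifies the mean and, with robust standard errors, gets its inference from large-sample behaviour of the estimate. It does not assume normal outcomes. Failing a skewness check is no reason to abandon it at this sample size.
2. **The destination is unclear.** There is no standard rank test equivalent to a covariate-adjusted time x group GEE. The usual substitutes compare arms at one visit or visits within one arm. They lose the adjustment, the interaction and the effect estimate on the planned scale.
3. **The choice comes after the data.** With no threshold, whether the primary model stands would be decided by someone looking at the outcome data.

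The stake is which test answers the trial's main question. One route, separate within-arm tests, can also suggest a benefit where the arms do not differ.

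**Working it through.** **Step 1. Reproduce the plan's own figure.** Inputs from Sample size estimation: effect size 0.5, power 0.80, two-sided 5%, attrition 14%.

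- Normal formula: n = 2(1.96 + 0.84)²/0.5² ≈ 63 per arm; 126/0.86 = 146.5, so 147.
- t-test version: 64 per arm; 128/0.86 = 148.8, so 149.

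Boths agree with the stated 150 to within 3 participants. The design is thus sized for a standardised difference in means between two arms, with about 150 × 0.86 = 129 completers, or 64.5 per arm.

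**Step 2. How often could the check fire?** The article gives neither a cut-off nor a distribution, so both are assumed here: gamma and log-normal data with coefficient of variation (CV) 0.5 to 1, N = 75 (one arm) and N = 150 (pooled), 4,000 simulated samples each. The standard error of skewness is √[6N(N−1)/((N−2)(N+1)(N+3))], which is 0.277 at N = 75 and 0.198 at N = 150. A z-rule at 1.96 therefore fires at an absolute skewness of only 0.54 or 0.39.

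| Rule assumed | Normal data | Gamma or log-normal, CV 0.5-1 |
|---|---|---|
| Skewness z above 1.96 | about 5% | 86-100% |
| Absolute skewness above 1 | 0% | 37-100% |
| Absolute skewness above 2 | 0% | 1-79% |

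A further assumed distribution (log-normal, log-SD 0.8-1.0, 10% zeros) gave 99.5-100% at a cut-off of 1 and 64-89% at a cut-off of 2. The answer is driven by the missing cut-off and the assumed shape.

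**Step 3. Does the planned contrast need normality?** With an identity link, complete data and no covariates, the time x group term for one follow-up against baseline is D = (mean change, intervention) − (mean change, control), with robust SE = √(v₁/n + v₀/n), where v is the variance of change in each arm. Reject when |D/SE| > 1.96. Assumptions: log-normal outcomes, correlation 0.5 on the log scale, n = 64 per arm, 20,000 simulated trials per row, the same distribution in both arms under the null.

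| CV | Type I error | Power at d = 0.5 |
|---|---|---|
| 0.5 | 5.4% | 80% |
| 1.0 | 4.9% | 76% |
| 1.5 | 4.9% | 76% |

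The error rate stays close to 5% under heavy skew. As a cross-check, an unequal-variance comparison of means on the log-normal data with 10% zeros gave a type I error of about 4%.

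**Step 4. What could a common substitute do?** Suppose a Friedman test is run separately in each arm over the three visits, and both arms change equally (normal data, correlation 0.5, 64 per arm, 2,000 simulated trials per row). The proportion of trials significant in the intervention arm only was:

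| Equal change in both arms | Significant in intervention arm only |
|---|---|
| 0 SD | 4.8% |
| 0.2 SD | 21% |
| 0.3 SD | 22% |
| 0.4 SD | 15% |

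That pattern could be read as a treatment effect in 15-22% of trials where the arms change alike. The article does not say this route would be taken; the result shows why the replacement cannot be left open.

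**The case against.** **The sentence may be aimed only at the baseline t-tests.** The normality check stands just before them, and the t-test is the named method that both assumes normality and has a textbook rank counterpart. This is a fair reading and cannot be ruled out. But the closing sentence speaks of analysing the data without restriction and comes after the GEE, so the wider reading is the natural one. If the narrow one was meant, the same short edit settles it.

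**A statistical analysis plan may supply cut-offs and tests.** That stands for the detail, and its absence from an article is not held against the trial. The point here is a rule that the article states. To protect the primary model, an analysis plan would have to override that sentence.

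A reader might also infer three stronger things that the documents do not support.

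- **That non-parametric methods cannot test time x group.** They can: a Mann-Whitney test on change scores, or a rank-based repeated-measures analysis, addresses it. The fault is that none is named and the common choices do not.
- **That the switch is very likely.** The Introduction reports inadequate activity in 56.7% of such patients in Sri Lanka. With an outcome bounded at zero this makes right skew plausible. But it is a yes/no prevalence from other studies, not a distribution of this outcome, and Step 2 shows how far the cut-off matters.
- **That the switch would cost power.** Under the assumed skew (log-normal with 10% zeros, single visit, unadjusted, multiplicative effect), Mann-Whitney had 64-65% power against 58-62% for the unequal-variance comparison of means. Where the check fires, a rank test may do at least as well.

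**Conclusion.** The point holds in limited form. As worded, an undefined normality check may replace the only hypothesis-testing model with unnamed methods after the data are seen, although that model with robust standard errors does not need normal outcomes at about 64 per arm. What is at risk is the pre-specification of the primary test, the covariate adjustment, and the time x group estimate on the planned scale.

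The simulated figures rest on assumed distributions, complete data and an unadjusted contrast. They support the claim that the switch is unnecessary for validity; they do not predict that it will happen. That the sentence reaches the GEE is the natural reading, not an explicit statement. The sample size is not affected. The change should be made before outcome data are examined, because it removes a post-data choice at almost no cost.

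**What to change.** - Limit the non-parametric fallback to the descriptive baseline comparisons and say so.
- State that the adjusted GEE with robust standard errors remains the primary analysis whatever the skewness, kurtosis and Q-Q checks show, and that these checks are diagnostics only.
- Name one sensitivity analysis for skewed outcomes in advance, for example the same model on log(x+1), or a bootstrap confidence interval for the time x group effect. Which one is a matter of choice; that it is fixed beforehand is what counts.

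The cost is a wording change and one extra run. The downside is that under strong skew the mean-based primary model may be less powerful than a rank test.

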#### Ethical consideration

Ethical approval was obtained from The Joint Chinese University of Hong Kong–New Territories East Cluster Clinical Research Ethics Committee (CREC Ref.No.: 2020.678-T) and Ethics Review Committee, Faculty of Health Care-sciences, Eastern University, Sri Lanka (E/2021/01). This trial protocol had been registered in ClinicalTrials.gov Protocol Registration and Results System (PRS) (NCT05051774). The study protocol adhered to the principles of the Declaration of Helsinki [44]. The approval was also obtained from the study hospital. The purpose of the study, data collection procedures, potential risks and benefits, maintenance of confidentiality, and voluntary basis of participation will be clearly explained to the participants. Written informed consent of the participants will be obtained from them. To ensure the participants’ confidentiality during the study, their names will be coded, and the codes will be stored separately to ensure anonymity. All electronic data will be stored by the principal investigator in a password-protected computer in a secured place. The paper records will be kept by the principal investigator in a locked cabinet. The personal data will only be accessed by the principal investigator. In addition, entered data will be cross-checked by a second person. All the data collected will be destroyed 5 years after the study is completed.

#### Potential risk management

Participants will be informed that there will be no cost for participating in this study, and it will not replace the health services provided by the healthcare professionals of the study hospital. The participants who refuse to continue the study for any given reason will be allowed to pull back from the study without any cost, and withdrawing from the study would not affect the amount of care they receive from the hospital. Participants will be asked to start the exercise at a low intensity and gradually increase in frequency, duration, and intensity. In addition, for continuing exercise at the patients’ homes, participants will be advised to continue the exercise performed in the previous week at the hospital. Moreover, participants will be encouraged to communicate with the researcher (registered nurse) whenever they need any information on CHD and to report any adverse events. Participants will be provided with an educational booklet about signs and symptoms that may develop during the exercise such as angina, dyspnea, tiredness, nausea, and vomiting, and symptom management information. If they develop any discomfort and have to seek medical help, they will be advised to stop the exercise immediately. Furthermore, an exercise self-evaluation form will be given to them to record their daily exercise in terms of frequency, duration, time, and intensity, and they will also be asked to write their self-perceived ideas about exercise to determine its progress. The emergency card with the research nurse’s name and contact information will be given to all participants for communication if they develop any discomfort due to exercise or disease deterioration.

## Discussion

This study aims to examine the effects of a motivated, action-based intervention consisting of three monthly supervised group exercises, group education, and individualized telephone follow-ups that are developed based on the HAPA framework and integrated with behavioral change strategies including improving exercise, following a healthy diet, and enhancing exercise self-efficacy to 1) improve physical activity, 2) enhance exercise self-efficacy, and 3) improve cardiovascular risk factors in patients with CHD in Sri Lanka. The intervention is developed based on the international recommendation for this population, and its cultural relevance to the Sri Lankan context is ensured using the national cultural appropriate recommendation to this population. This study encourages the participants to be actively involved with healthcare professionals in planning the action plan for behavioral change using the individualized risk assessment, goal setting, and awareness of the discrepancy between recommended guidelines and their daily activities. During their stay at their home, the individualized consultation of participants with the researcher or trained research assistant through telephone calls will serve as a communication platform in clarifying their doubts and supporting them to achieve the targeted goals in behavioral change. This study encourages the participants to share their experiences in behavioral change and support one another to motivate and achieve their goals.

As purported by the HAPA framework that underpinned the intervention of the current study, improving an individual’s exercise self-efficacy could lead to engagement in more physical activities. Self-efficacy plays a key role in behavior modifications, such as improving physical activity [23, 45, 46]. The intervention could enhance the self-efficacy of the intervention group during and after the intervention and might help them to overcome the barriers faced for continuing the physical activity at home. A systematic review of patients with CHD showed that listening to music significantly improved their adherence to exercise, facilitated to maintain the exercise after the intervention, improved exercise capacity, mood, cognition, and reduced perceived exertion [47]. In the current study, cultural music is used to facilitate the exercise of participants, which could help them to engage in more physical activities and maintain it after completing the intervention. In addition, music-faced physical activity improves the maintenance self-efficacy of the HAPA framework, thus could lead to a great improvement in the participants’ physical activities in the intervention group.

Supervised exercise training showed a significant improvement in several cardiometabolic outcomes, such as exercise capacity, body fat, BMI, and level of physical activity compared to non-supervised exercise training [48, 49]. The current study has provided supervised exercise training, which could encourage the participants to adhere to exercise, resulting in great improvement in their physical activity levels. Effective communication via mobile health is an effective approach in facilitating the patients with CHD to adhere to the exercise intervention as the secondary prevention of CHD [50, 51]. In the current study, participants will be communicated through telephone calls to strengthen their volition in performing the exercise at home and enhancing their problem-solving skills to overcome perceived barriers, continue the exercise, and reinforced any resulting positive changes.

### Limitations of the study

This study has some limitations. Although the participants for this study will be recruited from a university-affiliated teaching hospital in a district in Sri Lanka that provides extensive health services to the population with diverse socio-demographic and economic backgrounds, the general application of the findings may be limited because of the limitation of the population size in a certain district in Sri Lanka. Even though the study outcomes include objective blood parameters, there could be a risk for recall bias on the self-reported outcomes, such as exercise self-efficacy, which would be measured by a validated instrument.

## Conclusion

This study will be the first RCT to evaluate the culture-specific, motivated, action-based intervention coordinated by nursing health professionals in improving the physical activity level, exercise self-efficacy, and cardiovascular risk factors among patients with CHD in Sri Lanka. This study provides a unique and culturally relevant information to Sri Lankans and South Asians with similar cultural backgrounds on how to improve the modifiable risk factors among the CHD population. This study provides insights into which level this could be applicable with limited resources in developing counties like Sri Lanka where there is scarcity in accessibility and affordability of the comprehensive CR. In addition, this study informs healthcare professionals about exercise prescriptions for individuals who lack the time to engage in physical activity.

## Abbreviations

AACVPR: American Association of Cardiovascular and Pulmonary Rehabilitation
ACSM: American College of Sports Medicine
BMI: Body mass index
CESEI: Cardiac exercise self-efficacy instrument
CHD: Coronary heart disease
CR: cardiac rehabilitation
CVDs: Cardiovascular disorders
HAPA: Health action process approach
IPAQ-SF: International physical activity questionnaire short form
WHR: Waist hip ratio
